### 9.2.4 DESCRIPTIVE STATISTICAL METHOD

For the results of the questionnaires used:

- The number and percentage of participants (patients and professionals) with missing data will be described for each variable of interest. The reason for the missing data will be documented as much as possible in order to interpret the results.
- Qualitative variables will be described in terms of numbers, percentages and 95% confidence intervals according to the exact binomial distribution.
- Quantitative variables will be described in terms of numbers, means, standard deviations, medians, ranges and interquartile ranges.

For observations of consultations, systematically collected data will be described (duration of the different visits, delays between visits, characteristics of the professional(s) ...).

An analysis of the interviews will lead to a statistical approach of content, allowing to describe, among other things, the elements of understanding.

#### 9.2.5 COMPARATIVE STATISTICAL METHOD

The distributions of qualitative variables will be compared between groups by  $\chi^2$ , or corrected  $\chi^2$ , or Fisher exact tests, depending on the values of the expected numbers under the assumption of independence.

The distributions of quantitative variables will be compared between groups by the Student test if the conditions of validity of the test are respected (normal distribution, homogeneous variances). If the variances are unequal between the two groups, a Student test for unequal variances will be used and if the distribution is not normal, a Wilcoxon test will be used.

#### 9.2.6 QUALITATIVE DATA STATISTICAL METHOD

The interviews and the observation collections are sources of important content to be analyzed in order to study the themes addressed, the resemblance and heterogeneity between respondents, but also the evolution of the latter during the different phases of the study, while taking into account for the samples of patients the belonging to one or the other of the groups to see the differences.

#### 9.2.7 STATISTICAL SOFTWARE

The analyses will be carried out with R software (version 4.2.3 or later) and Nvivo software (version 9.4 or later).

### 9.3 ANALYSIS PLAN

#### 9.3.1 DESCRIPTION OF INCLUSIONS, DEVIATIONS AND FOLLOW-UP

The following elements will be presented:

- Verification of eligibility criteria,
- The study flow diagram following CONSORT recommendations,
- A description of the causes of death, abandonment, patients and professionals lost to follow-up or having abandoned the research, patients who were not operated on,
- Deviations from the protocol (particularly concerning deadlines),
- Follow-up visits carried out: number of patients having carried out each of the follow-up visits.

### 9.3.2 CHARACTERISTICS OF PATIENTS AT INCLUSION

Patients will be described according to the following variables:

- demographic characteristics,
- clinical characteristics, - biological characteristics,
- strategy characteristics.

### 9.3.3 ANALYSIS OF THE MAIN OBJECTIVE

The main objective is to study the effects of using a personalized 3D printed kidney model versus a generic 3D printed kidney model as a mediation tool, throughout the pathway, on the patient experience and their interactions with professionals, before and after partial nephrectomy.

The analysis of the main objective will be carried out by relying on the cross-referencing of elements from the different collection tools and will depend on the content of the interviews as well as observations. The analysis of the verbatims will be based on observational data and data from the questionnaires. A triangulation analysis of the data will therefore be carried out globally and then by group to study the differences.

A descriptive analysis will be carried out globally and by strategy group for patients on all data from the questionnaires, socio-demographic data as well as data characterizing the tumor. The description of the socio-demographic data of each of the two groups of patients (generic 3D model group / specific 3D model group) will be carried out: by indicating the frequencies (e.g.: sex, profession, etc.), the means and standard deviations (e.g.: age, illness delay, etc.) allowing the distribution of the two groups to be compared.

A comparison analysis between the groups of 3D model types will be carried out, systematically on the data from the questionnaires and the socio-demographic data.

The data from the interview transcripts will be analyzed in order to be able to study the unique life experiences of the patients as well as the common elements between patients and the heterogeneities between groups.

Observations and interviews are collection methods that do not automatically lead to a statistical analysis of the data. The statistical analysis will only cover part of the data collected, qualitative and quantitative.

The description of the patients' experience will be carried out based on the analysis of the contents of the interviews in a transversal manner for each time but also according to a longitudinal analysis taking into consideration the 3 times (T, T3 and T6) and specifying the group to which the patient belongs.

### 9.3.4 ANALYSIS OF SECONDARY OBJECTIVES

The description of interactions between professionals and patients, specifying the terms used and their frequencies, will be carried out via the analysis and synthesis of the information collected via the observation notebooks. This analysis will make it possible to respond to secondary objectives 1 and 2. Additional elements concerning patient and entourage interactions may come from interviews with patients and will enrich the response to objective 2.

To respond to the third secondary objective, a synthesis of all the information collected as part of the observations but also from interviews with patients and professionals will make it possible to trace the use made of 3D models and to understand the users and the circumstances of use.

The evolution of the understanding of the disease and surgery will be studied by analyzing the content of the interviews and the questionnaire on understanding renal anatomy and surgical issues with a tablet on UroConnect. The content will be compared between the two groups.

A descriptive analysis of the distribution of scores obtained by patients for the HLS-EU16 literacy questionnaire will be carried out in each group for times 1 and 6. A comparison analysis between time 1 and time 6 will be carried out, for each group, by a paired Student test, after checking the homogeneity of variances, otherwise non-parametric tests will be used. Finally, the changes between the two groups (HLSEU-Q16 at time T6 - HLSEU-Q16 at time T1) will be compared by a Student test.

A second analysis will be carried out using the classification of the literacy score into three levels as indicated in section 4.2, the data will be described for each time and then a comparison between times will be carried out by a paired Chi-square test.

A thematic content analysis of the interviews conducted with professionals will be carried out.

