### 2.2. SECONDARY OBJECTIVES

1. To use qualitative studies to describe interactions between professionals and patients, specifying the situations in which exchanges take place and their environments.
2. To use qualitative studies to analyse differences in discourse and the use of terms in the use of different tools during interactions between patients, professionals and their families.
3. To use a qualitative approach to study the use of the 3D-printed kidney model introduced during a medical information consultation right through to the post-operative visit.
4. To compare patient understanding of anatomy and surgical strategy according to the type of tool, personalised or generic, before and after the operation on the basis of questionnaires and interviews.
5. To compare the level of health literacy between the two groups and at different times (HLSEU-Q16: European Health Literacy Survey Questionnaire).
6. To use qualitative studies to describe the changes perceived by professionals in patient care following the integration of the mediation tool with patients. In order to meet the objectives set out above, the study will focus on two populations: patients and professionals.

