The evolution of the literacy score according to the type of mediation tool used during the information consultation will be assessed by measuring the HLSEU-Q16 at inclusion and 1 month post-operatively. This questionnaire is based on a model including four skills related to the processing of health information: access, understanding, evaluation and application of health information (Appendix 1). These four skills are explored in three health contexts: health care, disease prevention and health promotion. The HLSEU-Q16 is composed of 16 items. All dimensions are explored except for the dimension “applying information in health promotion”. This short version was validated in French by Rouquette et al. in 2018 (15). Each item is rated on a four-level scale: “very easy”, “easy”, “difficult” and “very difficult”. For the rating, the score of each item is reduced to a binary score, the “very easy” and “easy” modalities scoring for 1 while “difficult” and “very difficult” for 0. The total score can then vary from 0 to 16. To facilitate interpretation, they can be classified into three literacy levels: less than or equal to 8 reflecting an inadequate level, from 9 to 12 reflecting a problematic level and strictly greater than 12, an adequate level.

The distribution of the three score levels will be described preoperatively and postoperatively in each arm.

Validated in French, this short scale of the “European Health Literacy Survey Questionnaire” (14) has acceptable psychometric qualities and allows a reduced administration time for participants, the latter having several questionnaires to complete at the same time as part of the study.

Effects on professionals

Qualitative evaluation of changes in practices following the integration of 3D models into the practice of the service.

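### HLSEU-Q16: the arms are compared on unadjusted T6-T1 change, which loses precision against adjustment for the T1 score, and the within-arm paired test has the wrong assumption check

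*Protocol*

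**What the plan says.** Secondary objective 5 (Protocol 2.2) is "To compare the level of health literacy between the two groups and at different times". The instrument is the HLSEU-Q16, scored from 0 to 16 (3.2).

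Section 9.3.4 sets out three steps for it:

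- Within each group, T6 is tested against T1 "by a paired Student test, after checking the homogeneity of variances, otherwise non-parametric tests will be used".
- Between groups, "the changes between the two groups (HLSEU-Q16 at time T6 - HLSEU-Q16 at time T1) will be compared by a Student test".
- For the score cut into three levels, "the data will be described for each time and then a comparison between times will be carried out by a paired Chi-square test".

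Three other sections bear on the point:

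- Section 9.2.1 plans comparisons without adjustment and also with adjustment for initial prognostic factors that may be unbalanced despite randomisation.
- Section 9.2.5 gives the general between-group tests: chi-square or Fisher for categorical variables; Student, unequal-variance Student or Wilcoxon for quantitative ones.
- Section 9.3.3 adds: "A comparison analysis between the groups of 3D model types will be carried out, systematically on the data from the questionnaires".

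The T1 questionnaire is completed within 15 days of inclusion (7.4.1). The patient learns the allocation only at T2 (7.3.3).

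**The concern.** The T1 score is a baseline value of the outcome itself, taken before the patient knows which model will be shown. It is therefore a natural covariate. Subtracting it from T6 is a cruder use of it: the difference fixes the coefficient of T1 at 1, whereas a regression estimates it. When the true coefficient is below 1, the change score over-corrects and carries extra noise. With 30 patients per arm there is little precision to spare.

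The pre-check on the paired test is a separate matter. A paired t-test uses only the within-patient differences, so whether T1 and T6 have equal variances is irrelevant to its validity. As written, the rule can switch tests for a reason that does not matter (scores bunching near 16 at T6, for instance), and it does not ask for the check that does matter.

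**Working it through.** **Inputs from the protocol.** 60 patients, 30 per arm (9.1); 5% risk of error (9.2.3), taken here as two-sided; score range 0 to 16 (3.2). The protocol gives no SD, T1-T6 correlation, target difference or power for this score, so it has no figure of its own to reproduce.

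**Assumptions.** Equal SD s at T1 and T6; correlation rho from 0.3 to 0.9; s of 3 to 4 points where a result in points is wanted; a 0.5 SD difference for power.

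**1. Variance of the two analyses.** Per patient:

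- change score: 2s²(1-rho)
- T6 adjusted for T1: s²(1-rho²)
- ratio, adjusted to change: (1-rho²)/[2(1-rho)] = (1+rho)/2

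The extra patients that the change score needs for equal precision are 2/(1+rho) - 1. The difference detectable with 80% power at 30 per arm is (1.960 + 0.842) × sqrt(2/30) = 0.723 times the relevant SD. Power is by normal approximation.

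| rho | variance ratio | extra patients for change score | detectable difference in SD, change / adjusted | power for 0.5 SD, change / adjusted |
|---|---|---|---|---|
| 0.3 | 0.65 | 54% | 0.86 / 0.69 | 37% / 53% |
| 0.5 | 0.75 | 33% | 0.72 / 0.63 | 49% / 61% |
| 0.7 | 0.85 | 18% | 0.56 / 0.52 | 71% / 77% |
| 0.9 | 0.95 | 5% | 0.32 / 0.32 | 99% / 99% |

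A simulation with 30 per arm and normal data gave power of 36% against 51% (rho 0.3), 48% against 59% (rho 0.5) and 69% against 75% (rho 0.7), so the formula is a fair guide at this size.

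**2. In points of the score.** The 95% CI half-width is t × SD × sqrt(2/30), with 58 degrees of freedom for change and 57 for the adjusted analysis. The small term for chance imbalance in T1 is ignored.

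- rho = 0.5, s of 3 to 4: 1.55-2.07 on change, 1.34-1.79 adjusted.
- rho = 0.7, s of 3 to 4: 1.20-1.60 on change, 1.11-1.48 adjusted.

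**3. If the SDs differ.** With SDs s1 and s6, the change variance minus the adjusted variance is (s1² + s6² - 2·rho·s1·s6) - s6²(1-rho²) = (s1 - rho·s6)², which is never negative. The size of the gain depends on the equal-SD assumption. That adjustment does not increase the residual variance does not.

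**4. The paired-test condition.** In 40,000 simulated samples of 30 pairs with no mean change (normal data, correlation 0.5), the paired t-test rejected in 4.9%, 5.1% and 5.0% at T6/T1 SD ratios of 1, 2 and 3. Unequal variances at the two times leave its 5% level intact.

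**5. Whether section 9.2.1 already covers the first point.** Its adjusted analysis is tied to factors whose distribution may be unbalanced, and it does not name the T1 score. The gain in step 1 comes from the correlation of T1 with T6 and is there whether or not the arms look balanced at T1. A rule triggered by imbalance therefore does not guarantee it.

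**The case against.** The case for leaving the plan alone has weight. The change-score contrast between randomised arms is unbiased. If T1 literacy were visibly unbalanced and were treated as an initial prognostic factor, section 9.2.1 would bring in an adjusted analysis. The gain rests on assumed values: about 0.2 to 0.3 points of half-width at rho 0.5, about 0.1 at rho 0.7, and next to nothing near 0.9. The pre-check touches only the within-arm tests, which do not compare the models, and its effect is at most a move to a non-parametric test. The study is mainly anthropological, its main criterion is qualitative and it claims no power. All of this stands and limits the stakes. It does not make the variance check correct, and it offers no reason to prefer the less precise analysis when T1 is collected anyway.

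Three stronger readings are tempting, and the documents do not support them:

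- *That objective 5 is missed.* The Student test on change is itself a comparison between the groups, and the paired tests cover the comparison over time. The objective is addressed, though inefficiently.
- *That the three-level score is never compared between arms.* This is true only of the wording of section 9.3.4, which for the levels names a test between times. Section 9.3.3 commits to comparing the model groups on questionnaire data, and section 9.2.5 supplies the test for categorical variables. The comparison is implicit, not absent.
- *That regression to the mean or baseline imbalance biases the contrast.* Chance imbalance adds noise to a single trial's estimate, but under randomisation it does not shift the estimate on average.

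**Conclusion.** Two points hold. First, the unadjusted Student test on change gives up precision that adjustment for T1 would recover: the variance ratio runs from 0.65 at rho 0.3 to 0.95 at rho 0.9. The loss is material at rho of about 0.7 or below and negligible near 0.9. These figures assume equal SDs, and the rho values are not from the protocol. The loss is of precision only; the statement that there is no bias refers to groups as randomised. Second, homogeneity of variances is the wrong condition for a paired Student test, whatever SD or correlation is assumed. Neither point threatens the main conclusions of a mainly qualitative study. Both are stated choices in the protocol and worth correcting.

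**What to change.** In section 9.3.4:

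- Replace the Student test on changes by a linear model of the T6 HLSEU-Q16 score on arm and T1 score, fixed in advance and not dependent on observed imbalance. Report the adjusted mean difference with its 95% CI.
- For the within-arm comparison, delete the check on homogeneity of variances. Inspect the distribution of the T6-T1 differences instead, with the Wilcoxon signed-rank test as fallback.

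The cost is a change of wording and one degree of freedom in the model. No new data are needed, since T1 is already in the schedule.

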#### 10.1.2 RYTHME DES REUNIONS

The Scientific Research Council meets according to the needs of the study and at least once a year.

#### 10.1.3 ROLE

- Its mission is to make any important decision at the request of the coordinating investigator concerning the proper conduct of the research and compliance with the protocol.
- It verifies compliance with ethics.
- It obtains information from the Methodology and Data Management Center and the coordinating investigator center of the research on the progress of the research, any problems and the available results.

- It decides on any relevant modification of the protocol necessary for the continuation of the research, in particular:
  - measures to facilitate recruitment in the research,
  - modifications to the research documents (protocol and information and consent collection documents) before their presentation to the CPP,
  - measures that ensure the best security for people participating in the research, • discussion of the results and the strategy for publishing these results.
- The Scientific Council may propose to extend or interrupt the research in the event of too slow an inclusion rate, too many lost to follow-up, major violations of the protocol or for medical and/or administrative reasons. It specifies the possible modalities of the extended monitoring of the participants included in the research. - At the end of the meeting, the chair of the Scientific Council must inform the sponsor of the decisions taken. Decisions concerning a major modification or a budget modification must be approved by the sponsor.

## 10.2 INDEPENDANT SURVEILLANCE COMITEE

This study does not require the establishment of an independent monitoring committee due to the absence of any treatment that could lead to premature termination of the research and the nature of the procedures under study not entailing any significant risk for the patients.

## 11. MANAGEMENT AND PROCESSING OF SOURCE DATA AND DOCUMENTS

### 11.1 DONNEES ET DOCUMENTS SOURCES

Source data is all information contained in original documents, or in authenticated copies of these documents, relating to clinical examinations, observations or other activities carried out in the context of research and necessary for the reconstruction and evaluation of the research. The documents in which the source data are recorded are called source documents.

Need for UroCCR data

- Socio-demographic characteristics of the patient (age, sex),
- Tumor size,
- Tumor complexity score – RENAL,
- History of family cancer,
- Diagnosis of kidney cancer,
- Distance hospital home,
- Duration of the operation,
- Surgical history with general anesthesia, • Presence of an accompanying person during the consultation.

### 11.2 DATA COLLECTION INSTRUCTIONS

All information required by the protocol must be recorded in the medical record. Data must be collected as they are obtained and transcribed in a clear and legible manner. Medical data will be collected in the UroCCR database..

### 11.3 DATA MANAGEMENT AND CIRCUIT

### 11.3.1 DATA MANAGEMENT SOFTWARE

#### 11.3.1.1 SOFTWARE

eCRF for quantitative data: the software used for data management is an eCRF accessible at the following address: <https://uroccr.fr>

The IT maintenance and development of the eCRF are managed by CREDIM (Centre de Recherche et Développement en Informatique Médicale) which is an IT platform created within the University of Bordeaux.

UroConnect: The maintenance and development of the UroConnect application are provided by the company Resilience based in France (<https://www.resilience.care/>).

3D modeling: The software used for 3D modeling is Synapse 3D from Fujifilm.

Nvivo Pro for qualitative data: The data will be transcribed into a word processing document (.docx type) or directly within the qualitative analysis support software Nvivo Pro 13®, then analyzed via the Nvivo Pro 13® software.

#### 11.3.1.2 DATA HOSTING

CREDIM: The database management system used is Microsoft SQL server.

UroConnect: The data collected by UroConnect is stored in a service hosted in France (provider Eritel).

3D modeling: The 3D models are hosted on the servers or on the stand-alone computer with the Synapse 3D software, on the Bordeaux University Hospital server (NextCloud) then on the computer of the TechnoShop technician in charge of carrying out the 3D printing.

Qualitative data entry software:

The following documents relating to this research are archived in accordance with Good Clinical Practices and current regulations:

- The protocol and any modifications to the protocol: by the sponsor and the SHS research team,
- All other documents and letters relating to the research by the sponsor: the SHS research team.
- The notebooks: by the SHS research team within the CeDS laboratory.
- The other source data and transcribed data will be kept on the computers of the SHS research team for up to 5 years after the end of the ANR-21-RHUS-0015 project, i.e. 2032.

#### 11.3.1.3 DATA SECURITY

UroConnect: the data collected by UroConnect are stored in an HDS environment. eCRF for quantitative data: the server is located in a dedicated room, without windows. Entry to the secure room is by badge. The department doors are secured and locked in the evening. No computers are freely accessible, domain authentication is mandatory.

The management of access rights to the data collected by the eCRF is managed by CREDIM. Only the database managers, the project team and the auditors have direct access rights to the database.

The USMR will send CREDIM the list of people who must have access to the data. Statisticians and DMs will therefore have read-only access to the data.

Qualitative data (anonymized): all anonymized data (in audio or text or Nvivo format) will be stored on an external disk located at the CeDS, locked away for the duration of the study. The data will then be stored in archives on the University of Bordeaux network (CIRRUS system).

